#### 2.1.1. Trial Design

The study is designed as a prospective, randomized, controlled, triple-blinded, superiority clinical trial with two parallel groups and a primary endpoint of trochlear dysplasia screening and treatment over two months. Randomization will be performed as block randomization with a 1:1 allocation.

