#### 2.1.8. Outcomes

Outcomes measures will be collected two months after the first visit.

Primary outcome measures:The difference in the means of the sulcus angle between the two treatment arms at two months.

Treatment success is defined as a sulcus angle < 159° visualized by ultrasound. A sulcus angle ≥ 159° is the value set to diagnose TD in our study population, and values < 159° are considered non-dysplastic.

For newborns, radiographs and CT are not optimal imaging modalities. Besides X-ray radiation, the patellofemoral joint is not ossified, so it is not visible [36]. MRI is not an optimal screening tool because of the need for sedation, limited availability, and costs. Ultrasound allows for the visualization of cartilage and bone and is a faster, cheaper, and more available technique, so it could be used as a screening tool for detecting TD [37]. An ultrasound sulcus angle > 159° is considered dysplastic in newborns [28].

In our study, the ultrasound will be performed by a single observer in all cases to eliminate any possible inter-observer variability.

Secondary outcome measures:The difference in the means of the sulcus angle at baseline and after two months for each group;The difference will be measured by comparing the mean sulcus angle before and after the two-month treatment for the intervention group and the baseline and after two months for the control group.

The difference between the two treatment arms will be measured by comparing the proportion of patients in each treatment group with dysplastic (≥159°) and non-dysplastic (<159°) sulcus angles.

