#### 2.1.10. Sample Size

The study population are the newborns at TD of Virgen de la Arrixaca University Hospital. The total number of births in this institution in 2016 was 14,167. However, the frequency of TD in newborns is unknown.

Breech presentation is a risk factor for TD, and the frequency of breech presentation is between 3–5% [38]. We consider 5% to be the estimated frequency of this presentation at birth, which implies that approximately 708 newborns each year have a breech presentation in our population. TD (a pathologic sulcus angle) is identified in 10% of the breech presentation population [28]. Accordingly, we consider the number of newborns in our population with TD to be 71 per year.

For the ultrasound screening test, we need 116 ultrasounds to have a 95% confidence that the real value is within ±5% of the measured one. This estimation was calculated according to the following formula:$$n=\frac{\;\frac{Z_{\alpha }^{2}\cdot p\cdot \left(1-p\right)}{e^{2}}}{1+\left(\frac{Z_{\alpha }^{2}\cdot p\cdot \left(1-p\right)}{e^{2}\cdot N}\right)}$$
where *Z_α_* is the critical value of the normal distribution (for a confidence level of 95%, *α* is 0.05, and the critical value is 1.96), *e* is the margin of error (*e* = 5%), *p* is the sample proportion (*p* = 10%), and *N* is the population size (*N* = 708). Note that a finite population correction has been applied to the sample size formula.

For the estimation of the treatment groups sample size, the following formula is applied: $$n=\frac{2{\left(a+b\right)}^{2}\;\sigma^{2}}{{\left(\mu_{1}-\mu_{2}\right)}^{2}}$$
where *n* is the sample size in each group, a is the conventional multiplier for alpha, b is the conventional multiplier for power, σ is the sample variance, and *μ*_1_ − *μ*_2_ is the difference we aim to detect. The sample variance was calculated from a pilot study, from which we obtained a value of *σ* = 5.78.

To consider a difference of 10° in sulcus angles between the treatment and the control group as clinically significant (*μ*_1_ − *μ*_2_) and be detected with 80% power and a significance level alpha of 0.05, *n* = 5.25. That means six subjects per group is the minimum sample size.

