#### 2.3.3. Statistical Methods

The primary efficacy endpoint is the comparison of the treatment with the Pavlik harness for two months, measured by analyzing the initial ultrasound sulcus angle data and those obtained after the treatment period.

The Shapiro–Wilk test will be performed to assess the normality of data.

To determine if the Pavlik harness is more effective in reducing knee SA compared to no treatment, the results of the intervention group will be compared to the control group with the Student’s t-test for independent data. The intervention will be effective if it achieves statistical differences (with a 95% confidence) in the knee SA between the treatment and control groups before and after treatment.

To assess if the Pavlik harness is effective in reducing the knee SA within the treatment group, the Student’s t-test for dependent data will be applied to compare the values of the ultrasound sulcus angle at baseline and two months within each group (treatment and control).

A regression analysis will be performed to determine the relationship between the use of the Pavlik harness and knee SA while accounting for other factors that may affect the knee SA.

The difference in the proportion of participants between the two treatment arms who are classed as a treatment success at two months will be calculated with Fisher’s exact test of independence.

Missing data shall be treated using the multiple imputation procedure to identify patterns in the dataset’s missing data and replace missing values with plausible estimates.

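### At the stated minimum of six infants per arm, Fisher's exact test makes the secondary success comparison very conservative, and it cannot produce the difference in proportions that the plan assigns to it

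*Protocol article*

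**What the plan says.** Treatment success is a sulcus angle below 159° at two months (section 2.1.8). The same section lists, among the secondary outcomes, a between-arm analysis "comparing the proportion of patients in each treatment group with dysplastic" and non-dysplastic angles. Section 2.3.3 names the method: the difference in the proportion "classed as a treatment success at two months will be calculated with Fisher’s exact test of independence". It gives no sidedness, estimate or interval for this comparison.

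Section 2.1.10 sizes the trial for the mean sulcus angle only, for a difference to "be detected with 80% power and a significance level alpha of 0.05", and concludes: "That means six subjects per group is the minimum sample size". Allocation is 1:1 (section 2.1.1). The article gives no success rate for either arm and no power for the success comparison.

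**The concern.** There are two separate problems.

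- **Output.** The sentence names a quantity, a difference in proportions, and assigns it to a procedure that returns only a p-value. With so few infants, the estimated difference and its interval would be the most informative part of this analysis.
- **Efficiency.** Fisher's test conditions on the total number of successes. With six per arm few tables are possible, so the attained error rate falls far below 5% and power falls with it. Another exact test that also holds 5% recovers part of that power at the same sample size.

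At stake is the only between-arm analysis of the trial's own definition of success. Under the named test, a result in which all six treated infants normalise and two of six controls do so is not significant.

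**Working it through.** **1. The plan's own figure.** Inputs from section 2.1.10: difference 10°, SD 5.78, 80% power, alpha 0.05.

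n = 2(1.960 + 0.842)² × 5.78² / 10² = 2 × 7.851 × 33.408 / 100 = 5.25, so six per group.

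This reproduces the stated value. A one-sided multiplier would give 2(1.645 + 0.842)² × 33.408 / 100 = 4.13, so five. The sample size is therefore two-sided, and the rest of this check uses two-sided 5%.

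**2. Which tables reject at 6 against 6.** All 49 outcome pairs were enumerated. The Boschloo p-value is the largest probability, over a common success rate, of a table with a Fisher p-value no larger than the one observed. The pairs below, and their mirror images, are those that either test rejects.

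| Successes | Fisher p | Boschloo p |
|---|---|---|
| 6 vs 0 | 0.002 | 0.0005 |
| 6 vs 1, 5 vs 0 | 0.015 | 0.006 |
| 6 vs 2, 4 vs 0 | 0.061 | 0.021 |
| 5 vs 1 | 0.080 | 0.039 |

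Fisher rejects only the first two rows. Boschloo rejects all four.

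**3. True size.** The maximum is at a common rate of 0.5, where each pair has probability C(6,i) × C(6,j) / 4096.

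- Fisher: 2 × (1 + 6 + 6) / 4096 = 26 / 4096 = 0.63%.
- Boschloo: 2 × (1 + 6 + 6 + 15 + 15 + 36) / 4096 = 158 / 4096 = 3.86%.

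**4. Power at assumed rates of 80% and 20%.** With six infants, the probabilities of 6, 5 and 4 successes at 80% are 0.2621, 0.3932 and 0.2458. By symmetry these are also the probabilities of 0, 1 and 2 successes at 20%.

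- Fisher: 0.2621² + 2 × 0.2621 × 0.3932 = 0.275.
- Added by Boschloo: 2 × 0.2458 × 0.2621 + 0.3932² = 0.283, total 0.558.

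Other assumed rates at six per arm, Fisher against Boschloo:

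| Success rates | Fisher | Boschloo | Ratio |
|---|---|---|---|
| 90% vs 20% | 44.1% | 73.7% | 0.60 |
| 90% vs 10% | 65.9% | 88.9% | 0.74 |
| 95% vs 5% | 88.2% | 98.0% | 0.90 |
| 50% vs 5% | 8.4% | 27.9% | 0.30 |

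**5. Power under the protocol's own effect.** The success rate in an arm is Φ((159 − mean) / 5.78), with the treated mean 10° below the control mean. Normality, a common SD and the control mean are assumptions. For a control mean of 164° the rates are Φ(−0.865) = 19.4% and Φ(0.865) = 80.6%.

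| Control mean | Fisher | Boschloo | Ratio |
|---|---|---|---|
| 162° or 166° | 24.6% | 53.0% | 0.46 |
| 164° | 29.4% | 58.1% | 0.51 |
| 168° | 13.9% | 38.2% | 0.36 |
| 170° | 4.9% | 19.8% | 0.25 |

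**6. Dependence on n, at 80% against 20%.**

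| n per arm | Fisher | Boschloo | Relative loss |
|---|---|---|---|
| 6 | 27.5% | 55.8% | 51% |
| 7 | 44.8% | 49.6% | 10% |
| 8 | 59.8% | 61.4% | 3% |
| 10 | 63.5% | 80.5% | 21% |
| 12 | 81.2% | 84.8% | 4% |

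**The case against.** Fisher's test is a standard choice for small 2×2 tables and keeps the error rate below 5%. The comparison is secondary, and the article claims no power for it, so no stated figure is contradicted. All of this stands, and it limits the point to efficiency and reporting.

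Three stronger readings are tempting, and the document supports none of them.

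- **That Fisher halves the power in general.** Six is a minimum, and section 2.1.10 estimates 71 affected newborns a year. The loss at six per arm runs from about 10% to 75% over the rates examined. At 80% against 20%, one more infant per arm cuts it from 51% to 10%. Part of the gap at six is discreteness: Boschloo's own power falls between six and seven per arm.
- **That the true error rate is below 1%.** This needs exactly six per arm and a two-sided test. At seven per arm the maximum is 1.29%. Run one-sided at 5% with six per arm, it is 79 / 4096 = 1.9%. Section 2.3.3 does not state the sidedness of this test.
- **That the size of the effect would go unreported.** Section 2.1.8 compares the proportions in each arm, so both, and hence their difference, would be available. An interval method may also be left to an analysis plan that is not shown. What remains is that the sentence in section 2.3.3 assigns the difference to a test that does not produce it.

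It is also fair to say that a better test does not rescue the comparison: at six per arm Boschloo still has only 56% power for a 60-point difference. That is no reason to keep the weaker test, because Boschloo rejects every table that Fisher rejects.

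**Conclusion.** The point holds as an inexpensive improvement to a secondary analysis. It is not an error-rate violation, and it does not touch the primary comparison of means.

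The sentence in section 2.3.3 misstates what Fisher's test delivers, whatever the sample size. The size figures (0.63% against 3.86%) are exact for six per arm, two-sided 5%. The power figures rest on success rates that the article does not give: 27.5% against 55.8% if they are 80% and 20%, and 5–29% against 20–58% under the protocol's 10°, SD of 5.78 and 159° cut-off, with normality and control means of 162° to 170° assumed. With more than six per arm the gap is usually smaller but uneven. In the cases computed from six to twelve per arm, Boschloo was never less powerful than Fisher.

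**What to change.** In section 2.3.3, before any outcome data are seen, replace the sentence on Fisher's test with wording such as: *The between-arm difference in the proportion of infants with a two-month sulcus angle below 159° will be reported with a 95% confidence interval (exact unconditional or Newcombe) and tested with Boschloo's exact unconditional test, two-sided at 5%.* Settle on one of the two interval methods at the same time. Fisher's p-value may be kept, at most as supportive. Timing matters, because a change of test after seeing 4/6 against 0/6 would not be credible.

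The cost is one sentence. No extra infants, visits or procedures are needed, and the primary analysis is unchanged. The small downside is a test that is less familiar to readers, though it is available in standard software.

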#### 2.1.5. Modifications

The patient will be monitored for concomitant pathologies that have arisen during treatment with the Pavlik harness to assess whether they will cause discomfort or difficulty for the patient and their family. In case of incompatibility, treatment with the Pavlik harness will be withdrawn.

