## 3. Discussion

TD is a condition identified late and usually requires an invasive treatment when symptomatic.

The possibility of TD being a developmental entity could attain its early diagnosis before patients become symptomatic during adolescence or early adulthood when it is too late for the skeleton to remodel, usually requiring aggressive surgical interventions.

Developmental dysplasia of the hip is a condition that presented a prognosis similar to TD before the introduction of the Pavlik harness. Both conditions have been associated [23,27], so it is plausible to assume they share some common risk factors. In our study, we hypothesize that the breech presentation is a risk factor for TD, as shown in previous human [28] and animal [26] studies. In DDH, a subluxated or dislocated femoral head precipitates the development of a shallow and abnormal acetabulum. Likewise, an extended leg during the breech fetal position could play a similar pathological process as a lack of mechanical forces on the femoral trochlea could precipitate the development of a shallow trochlear sulcus. Thus, we decided to select the newborns in breech presentation as a target group to obtain sonographic data to define radiological values for the dysplastic trochlea. This would serve as a guide for a future screening method that would help identify TD early.

Given that TD may be a developmental process, early diagnosis in the neonatal period could allow for an intervention such as DDH. The Pavlik harness is a treatment option that would maintain the knees bent using the patella to help mold the trochlea in a similar way it is used to make the femoral head mold the acetabulum. Although safe, this treatment is not exempt from certain difficulties in the daily tasks of caring for the newborn, such as nappy changing or dressing. This manifests as a struggle to convince the caregivers of the patient of the future benefits of the Pavlik harness and for compliance, as TD is a condition that usually manifests later in life; thus, the results are not tangible in the short term.

We will conduct a randomized controlled trial to validate the hypothesis that trochlear dysplasia can be treated non-invasively early in life with a Pavlik harness.

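### The 80% power is 77% for the planned t-test with no loss and lower with any loss, and multiple imputation of the two-month angle makes the primary test worse than using the observed scans

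*Protocol article*

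**What the plan says.** Section 2.1.10 (Sample Size) applies the normal-approximation formula for two means. The target is set out as "To consider a difference of 10° in sulcus angles between the treatment and the control group as clinically significant", to "be detected with 80% power and a significance level alpha of 0.05". On the spread it says "The sample variance was calculated from a pilot study, from which we obtained a value of" 5.78. The result is n = 5.25, and the section concludes: "That means six subjects per group is the minimum sample size". No inflation for loss follows, and no loss rate is given. Section 2.1.1 adds "Randomization will be performed as block randomization with a 1:1 allocation".

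Section 2.3.3 (Statistical Methods) names Student's t-test for independent data as the comparison between arms. Its rule for missing values is unconditional: "Missing data shall be treated using the multiple imputation procedure to identify patterns", followed by replacement with plausible estimates. Section 2.1.8 (Outcomes) has outcomes collected once, two months after the first visit.

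Two other places bear on how likely loss is. Section 2.1.5 (Modifications) says "In case of incompatibility, treatment with the Pavlik harness will be withdrawn". The Discussion says "This manifests as a struggle to convince the caregivers of the patient of the future benefits of the Pavlik harness and for compliance".

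**The concern.** The stated power holds at best if every randomised infant has a two-month angle. With 12 infants, one missing scan is over 8% of the data (1/12 = 8.3%), so the rule for a missing primary outcome matters more than in a larger trial.

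The rule chosen is weak here. There is no intermediate angle, so an infant without the two-month scan brings only the baseline angle and covariates recorded at entry. Imputing the outcome from these gives nothing that a model containing the same covariates would not get from the observed infants. What imputation does add is noise between imputations, with the residual variance estimated from about 10 or 11 infants. The usual large-sample pooling rule is also not reliable at this size. The sentence further gives multiple imputation the job of finding patterns of missingness, which it does not do.

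The primary test could therefore have less power than the observed scans alone would give, or a false-positive rate above 5%, while the article's only printed power figure is 80%.

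**Working it through.** **Inputs from section 2.1.10:** difference 10°, SD 5.78 (called a variance in the text but squared in the formula), alpha 0.05, power 80%, six per group. Sidedness is not stated; two-sided reproduces the plan's figure. The infant is taken as the unit.

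**1. The plan's own figure.** n = 2(1.96 + 0.842)² × 5.78² / 10² = 5.25, rounded up to 6. The figure is reproduced.

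**2. Power of the planned t-test.** The non-centrality is (10/5.78) / √(1/n₁ + 1/n₂), with n₁ + n₂ − 2 degrees of freedom.

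| Infants scanned at two months | df | critical t | non-centrality | power |
|---|---|---|---|---|
| 6 + 6 | 10 | 2.228 | 2.997 | 77% |
| 6 + 5 | 9 | 2.262 | 2.857 | 72% |
| 5 + 5 | 8 | 2.306 | 2.736 | 67% |
| 5 + 4 | 7 | 2.365 | 2.579 | 60% |
| 4 + 4 | 6 | 2.447 | 2.447 | 54% |

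The normal approximation gives 85% at 6 + 6, which is why six looked sufficient. The t-test needs seven per arm to pass 80% (84%).

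**3. Multiple imputation with one loss per arm.** The article gives no imputation settings, so these are assumptions: bivariate normal baseline and two-month angles with correlation ρ; scans missing at random; proper Bayesian regression imputation on arm and baseline; 20 imputations; t-test estimate pooled by Rubin's rules; 6,000 simulated trials per setting (Monte Carlo standard error about 0.6 points for power, 0.3 for error rate).

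| Analysis | ρ = 0.3 | ρ = 0.5 | ρ = 0.7 | type I error |
|---|---|---|---|---|
| Imputation, Barnard-Rubin df | 56.1% | 58.9% | 63.2% | 3.1–3.4% |
| Imputation, classical Rubin df | 71.3% | 73.6% | 76.4% | 6.6–6.9% |
| t-test on observed scans | 66.9% | 66.9% | 66.9% | 5.1–5.2% |
| Observed scans, baseline as covariate | 63.5% | 71.7% | 86.1% | 5.0% |

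A second simulation with 20,000 trials per setting and 20 imputations gave 56.5%, 59.7% and 64.3% with small-sample df (error 3.3–3.6%), and error 6.7–7.0% with classical df. The higher power in the second row comes with an error rate above 5%.

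**4. Other loss patterns (second simulation, small-sample df, across imputation settings).** One infant lost in total: 64–71%, against 72% on observed scans. Two lost per arm: 31–46%, against 54%.

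**5. Splitting the fall at one loss per arm.** From 80% to 77% is the sample size formula (3 points). From 77% to 67% is the lost scans (10 points). From 67% to 56–63% is imputation with small-sample df (4–11 points).

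**6. Chance of any loss.** With an assumed loss rate d, the chance that at least one of 12 scans is missing is 1 − (1 − d)¹²: 46% at 5%, 72% at 10%, 93% at 20%.

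**The case against.** - **The plan does not predict missing scans.** This stands. A reader might infer from harness withdrawal and from the Discussion that missing two-month angles are expected. Section 2.1.5 withdraws the treatment and does not cancel the ultrasound. The Discussion speaks of persuading caregivers and of compliance. The imputation sentence is a contingency with no rate attached.
- **Imputation does not take power from 80% to 56–63%.** This also stands. A reader might take that fall as a general effect of imputation, but step 5 shows that much of it comes from the formula and from the lost scans. The range also holds only under the settings in step 3.
- **Imputation details belong in an analysis plan.** Their absence is no fault, and the article does not prescribe the classical pooling rule. But the choice of method is fixed in the article, and under neither pooling rule does it match the observed-data analysis: one loses power, the other exceeds 5%.
- **Six is called a minimum.** More could be enrolled, but no higher target is given. The planned 116 screening ultrasounds at 10% prevalence yield 11.6 dysplastic infants, about 12, before exclusions and refusals.
- **More than a baseline angle is recorded.** Section 2.3.1 lists age, sex, birth weight, breech type and hip status, and section 2.1.9 has both knees scanned. One knee might be measured when the other is not, and the rule also covers missing covariates. The point here is confined to an infant with no two-month angle.
- **Adjusting for baseline can cost power.** True at low correlation: 63.5% against 66.9% at ρ = 0.3.

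**Conclusion.** The point holds in a limited form. The 80% is 77% for the planned two-sided t-test with every infant scanned, and 72%, 67% and 54% with one infant lost, one per arm and two per arm. These figures follow from the plan's own inputs with the infant as unit.

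Multiple imputation of the single post-baseline outcome then makes the primary test worse than using the observed scans. With one loss per arm, imputation on arm and baseline, and correlation 0.3–0.7, power is about 56–63% at an error rate near 3%, or the error rate is about 7%. The error inflation is modest and arises only with classical degrees of freedom. The size of the effect is conditional on assumptions that the article does not settle. The direction was the same in the loss patterns examined.

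**What to change.** **Section 2.3.3.** Replace multiple imputation of the two-month angle by an analysis of all observed two-month angles by randomised arm, with baseline angle as covariate. This is valid when missingness depends on arm and baseline, provided the model holds. Add a bounding sensitivity analysis in which missing harness infants are given their own baseline angle and missing controls a favourable value.

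**Section 2.1.10.** State that the unadjusted t-test has 77% power with six scanned infants per arm, and print 67% and 54% for one and two losses per arm. Label all three as unadjusted t-test powers, since they are not the powers of the baseline-adjusted analysis.

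**Cost.** A few sentences and one small sensitivity analysis, with no extra infants or procedures. The printed power is less favourable, and power is slightly lower than for the unadjusted t-test if the baseline correlation is low. The change does not restore 80% power at six per arm; it makes the stated figure accurate and avoids a further loss.
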